#### End visits (WUR-*T*_1_, ZGV-*T*_1_)

2.6.4

The end visits at WUR-*T*_1_ (week 25) and ZGV-*T*_1_ (week 26) as well as the week between the two visits, follow the exact same procedure as the baseline visits. Standardised meals will be delivered to participants’ homes in week 24. At the final ZGV-*T*_1_ visit, participants will hand in their supplement containers and compliance diaries for adherence verification, and provide feedback on smartwatch use and overall study participation.

### Interventions

2.7

#### Rationale for the choice of comparators

2.7.1

To capture a broader spectrum of potential health benefits in the SCD + population, this study includes three distinct dietary fibres, each differing in carbohydrate classification and physicochemical properties (Table 5). Given their structural diversity, varied mechanisms of action and gut-brain effects are anticipated (128). The fibres, and their dosages have been carefully selected based on existing evidence, as is described in section below. To date, none of these studies have been performed in SCD(+).

**Table 5 tab5:** Overview of investigational products and dosages.

Intervention	Carbohydrate classification	Dosage	Composition (per 100 g)		Potential Effects
Chicory Inulin	Inulin-type fructan (soluble fibre)	12 g/day (6 g bid)	**Fibre**	**90 g**	↑ SCFAs, ↑ BDNF, ↓ Inflammation, ↑ Memory and Mood, ↑ Beneficial microbiota, ↑ TRP- derived indoles, ↑ Intestinal barrier function
			Energy	839 kJ/ 208 kcal	
			Carbohydrates	97 g (of which sugars 7 g; 90 g fibre)	
Resistant Dextrin	Glucose-oligosaccharide non-digestible (soluble fibre)	14 g/day (7 g bid)	**Fibre**	**82 g**	↑ SCFAs, ↓ Cortisol, ↓ Insulin resistance, ↑ Beneficial microbiota, ↑ TRP-metabolite ratios, ↑ Intestinal barrier function
			Energy	896 kJ/ 220 kcal	
			Carbohydrates	14 g (of which sugars <0.5 g)	
Seaweed polysaccharide (β-glucan and Fucoidan)	Hemicellulose + Non-starch polysaccharide	1 g/day and 7 g/day maltodextrin (500 mg and 3.5 g bid)	**Fibre** ^ **1** ^	**39.6 g**	↑ SCFAs, ↑ BDNF, ↓ (Neuro)inflammation, ↑ Beneficial microbiota, ↑ Intestinal barrier function
			Energy^1^	1,090 kJ/ 262 kcal	
			Carbohydrates^1^	58.22 g (of which sugars 0.1 g)	
			Fat^1^	1.6 g	
			Protein^1^	26.08 g	
Placebo (Maltodextrin)	Short-chain digestible oligosaccharide	7 g/day (3.5 g bid)	**Fibre**	**0 g**	Used in dietary fibres studies, minimal colonic fermentation
			Energy	1,641 kJ /386 kCal	
			Carbohydrates	96 g (of which sugars 6 g)	

^1^Composition/100 g of seaweed polysaccharide, without addition of maltodextrin.

Inulin as a soluble, non-viscous dietary fibre extracted from chicory roots (129), is recognised as a prebiotic by ISAPP (130), as well as having an European Food Safety Authority (EFSA) approved health claim, relating to gastrointestinal function (129, 131, 132). Resistant dextrin (RD) is also a soluble non-viscous dietary fibre derived from starch that selectively modulate microbiota and offers proven health benefits including blood glucose management (88, 133, 134). Seaweed and macroalgae are emerging as sustainable food sources and contain ß-glucans (135). All three fibres may provide promising novel leads in neurodegenerative diseases (93, 136). Maltodextrin is frequently used as a placebo in human studies and has been used as placebo in inulin, RD and *β*-glucan studies (88, 137, 138).

#### Evidence summary of investigational products

2.7.2

##### Investigational product 1: chicory inulin

2.7.2.1

In preclinical studies, inulin and inulin-type fructan supplementation resulted in improved cognitive function and mood with antidepressant and anxiolytic effects, enhanced neurogenesis and synaptic plasticity via upregulation of BDNF signalling, and improved BBB permeability (92, 139). Furthermore, studies demonstrated neuroprotective effects and modulation of neuroinflammation in AD models (140). In terms of gut health, SCFA production and beneficial tryptophan (TRP)-derived metabolites, including beneficial indoles (IPA), were increased (139–141), with reductions in inflammatory cytokines seen in both colon and the brain (92). Changes in gut health parameters, including microbiota composition changes, were associated with beneficial cognitive outcomes in a number of studies, highlighting the role of the MGBA (17, 92, 94, 139).

Consistent with preclinical studies, human studies have also shown beneficial effects of chicory inulin type-fructans (ITFs) on both gut health (19, 89) and cognition (19, 22, 23). Alterations in gut microbiota composition were shown after 1–4 weeks (19, 89, 97) notably, with higher abundances of beneficial *Bifidobacterium* (142). Additional findings include increases in faecal SCFA (91, 143, 144), acute increases in plasma 13C-SCFA (145) and improved intestinal barrier function with changes in tight junctions (146). Specifically, increases in SCFAs were seen in older adults. (144). Effects on brain health have been shown in acute (4 h) or longer term (2–36 weeks) ITF supplementation, including improved episodic memory performance (immediate and delayed) (23), cognitive flexibility (21), mood (19, 21, 23), and overall mental wellbeing (97).

*Risks and benefits*

Inulin is a well-tolerated prebiotic (147). Mild gastrointestinal side effects are reported at higher bolus doses (128, 142). Clinically supported benefits include improved stool frequency (132), glycaemic regulation (148), and emerging brain health effects (23, 76). The European Commission has approved the use of a chicory inulin product for the health claim “chicory inulin contributes to maintenance of normal defecation by increasing stool frequency” (131).

##### Investigational product 2: resistant dextrin

2.7.2.2

Pre-clinical studies of RD have demonstrated effects on gut health by modulating microbiota composition and increasing SCFA production (133, 149–152). Evidence for cognitive effects remain sparse, with one study showing supplementation of RD or RD combined with maltitol, resulting in improved vigilance and cognitive discrimination performance, independent of glycemic response differences (96). In an *in vitro* study, 7 g given twice daily for 18 days increased total bacterial counts and key butyrate-producing taxa (*Clostridium cluster XIVa, Roseburia*), along with elevated levels of acetate, propionate, and butyrate (150). Similarly, 14 days of RD supplementation in rats increased all three major SCFAs (152). In mice fed a high-fat, high-fructose diet, 10 weeks of RD gavage (5 g/kg) enhanced the abundance of *Prevotella* and *Akkermansia*, reduced serum insulin, and improved lipid profiles. (133).

In clinical studies, RD has demonstrated gut health effects by modulating microbiota composition such as increases in *Bacteroides*, *Parabacteroides* and inhibition of *Clostridum perfringens* (72, 88, 153, 154), while increasing SCFAs (72). Studies also demonstrated a reduction in endotoxemia (LPS) levels (20, 155, 156). In terms of brain health, RD has shown improvement in sleep quality (156), depression and anxiety, as well as reduction of cortisol levels (155, 156), modulation of insulin resistance (20, 155) and alteration of tryptophan metabolite ratios (20, 156). Higher cortisol has been previously associated with poorer overall cognitive functioning and MCI, where altered hypothalamic pituitary adrenal (HPA) axis, is proposed to underly neurotoxicity (157). Insulin resistance has been cited as predictive marker of cognitive decline (158) and beneficial tryptophan metabolites may modulate neuroprotective effects along the MGBA (159, 160).

*Risks and benefits*

Resistant dextrin may potentially cause gastrointestinal discomfort as its main side effect. No other known risks have been demonstrated. Potential benefits of resistant dextrin include gut and brain health effects (88, 150, 154–156), regulation of glycaemic responses and improved insulin resistance, increased satiety and reduction of energy needs (133, 134) Studies show no demonstrable side-effects at high dosages (161).

##### Investigational product 3: seaweed polysaccharide

2.7.2.3

The investigational product contains *β*-glucan and fucoidan (a seaweed polysaccharide).

Supplementation with both β-glucan and fucoidan individually demonstrated MGBA effects in preclinical models. Gut health effects include beneficial microbiota composition changes (*Bacteroidetes, Lactobacillus, Bifidobacterium, Akkermansia*) (16, 162) increased *α*-diversity (163, 164) and increases in faecal SCFAs (16, 163, 164). Furthermore gut barrier integrity was improved by upregulation of tight junctional proteins (162, 163, 165), strengthening of the mucosal barrier (163, 165, 166) and reduced colonic inflammation (165). Both supplements have demonstrated cognitive effects including improved memory and spatial learning, alongside optimised synaptic and signalling pathways (16, 162, 166). Behavioural changes were also seen with reduced anxiety (164, 167–169). Results indicated that memory function improvement was mediated by increases in BDNF levels (164, 166), and improved insulin signalling (164). Supplement-specific results of *β*-glucan include reduced hippocampal microglia activation (162, 166), improved synaptic ultrastructure (162, 166) and reduced tau hyperphosphorylation (16, 162), while fucoidan has demonstrated neuroprotective effects against Aβ aggregation, plaque formation (167) and Aβ-induced neurotoxicity (170).

In clinical studies, evidence of β-glucan and seaweed effects on the MGBA are still being explored. A recent study of a fucoidan-rich extract derived from *Saccharina latissima* (sugar kelp) in healthy adults, demonstrated increased abundance in beneficial *Bifidobacterium, Faecalibacterium*, and *Lachnospiraceae*, with reduced pro-inflammatory taxa. Further *in vitro* simulations showed dose-dependent increases in SCFAs (87). Additional studies support the effects of fucoidan on intestinal health, with co-supplementation in chronic superficial gastritis resulting in reduced gastric mucosal damage, reduced intestinal inflammation, increased SCFAs, improved gastrointestinal symptoms, and increases in *Bifidobacterium* and *Bacteroides* (171). Studies in prediabetes and *H. Pylori* eradication further demonstrate beneficial effects on microbiota composition as well as reduced systemic inflammation (172, 173). Gastrointestinal benefits of *β*-glucan have also been seen in healthy adults with supplementation demonstrating improved microbiota composition accompanied by increases in SCFAs (174). In terms of cognition, two β-glucan studies demonstrated effects on mood as well as improvements in overall well-being (24, 25), while *Laminaria japonica* (Japanese kelp) enriched with GABA, resulted in improvement in neuropsychological test scores (short-term memory, executive function, intelligence, sensory memory capacity) in senior subjects, with significant increases in BDNF (122).

*Risks and benefits*

No side effects to β-glucans have been reported in clinical trials (137). Daily intake of fucoidan at the intervention dosage has been established as safe (175).

#### Intervention description

2.7.3

The study has three treatment arms (chicory inulin, resistant dextrin and seaweed polysaccharide) and one placebo arm (maltodextrin). All supplements will be provided in powdered form and will be consumed in the same manner, namely mixed in 200 mL water, coffee or tea, at breakfast and dinner, taken as close as possible to the same time per day. All products and placebo dosages are matched iso-calorically and have been weighed and filled in sachets by a commercial company. Compliance will be monitored by completion of a compliance diary.

To reduce the possibility of side effects the daily dosage is halved, to be taken twice a day. Additionally, to allow for intestinal adaptation to increased fibre intake, participants only consume half of the daily dosage during the first week of the study, followed by the full dosage from week two onwards. Elderly individuals may be more prone to gastrointestinal sensitivity, and the chosen dosages minimise the risk of side effects, while in keeping with dosages for anticipated brain health effects.

##### Interventional product 1: chicory inulin

2.7.3.1

The chicory inulin powder is a commercially available powder from Sensus (the Netherlands). The powder is a native inulin, extracted from chicory roots. The agglomerated powder has an excellent dispersibility and wettability. The product has a neutral taste and is readily dissolved in water. Previous studies conducted that had positive effects on cognition include dosages of 5 g (19, 23), 10 g (22) and 16 g (21) per day. Effects on gastrointestinal microbiota were observed at dosages from 2.5 g to 20 g (176–178). A dose of 12 g/day is chosen which is approximately in the middle of the doses that found an effect on cognition. No adverse effects were shown at this dose, but mild flatulence can occur for some individuals (147, 179).

##### Investigational product 2: resistant dextrin

2.7.3.2

The resistant dextrin powder is commercially available from Roquette (France). The product is a low viscosity soluble fibre, made from wheat through a highly regulated dextrinization process accompanied by chromatographic fractionation (180). The dextrin is poorly digested and absorbed in the ileum, and thus largely available for colonic fermentation (72, 161). The product has a neutral taste and is readily dissolved in water. Gastrointestinal tolerance has been shown at high doses (161). Additionally, the effects of the investigational product in a compote (pea protein, hydrolyzed wheat gluten) was evaluated in elderly (70–90 years), with good digestive comfort and gastrointestinal tolerance (181).

##### Investigational product 3: seaweed *β*-glucan extract

2.7.3.3

The seaweed investigation product is a non-commercially available product from Oceanium (Scotland). The product consists of a *β*-glucan and fucoidan mixture, isolated from brown seaweed (*Laminaria saccharina,* sugar kelp). Purity assay analyses reported the supplement to contain 66.3% β-glucan, 9.24% fucoidan, 10.27% protein, 2.28% ash and 1.49% alginate on average. Preparation of β-glucan and fucoidan was performed by water-based extraction methods without chemical modification. *Saccharina latissima* (Linnaeus) is one of the dominant kelp-forming species of brown macroalgae in Europe. The seaweed for the product is sustainably farmed in the north Atlantic (182). The seaweed product is fully dissolvable in water. The product has a beige/brown appearance with a toasty/malty odour and taste. The chosen fucoidan dosage has been established as safe (175). Additionally, previous studies of 250 mg/day of *β*-glucan demonstrated effects on mood (24, 25). To ensure volumetric and caloric equality with the placebo arm, 3.5 g twice a day (7 g/day) of placebo (maltodextrin) has been added to the product.

##### Investigational product 4: placebo: maltodextrin

2.7.3.4

Maltodextrin (Roquette, France) will be used as the placebo in this study. Maltodextrin is frequently used as placebo in human studies, and has been used as placebo in inulin, RD and β-glucan studies before (88, 137, 138). The maltodextrin product is produced by hydrolysis, purification and spray-drying of edible maize starch. The chosen placebo is a short-chain maltodextrin (dextrose equivalent of 18.0–19.9), allowing for readily absorption in the small intestine, and thus virtually eliminates potential prebiotic or fermentative effects in colon. The product is a white powder and has a neutral/slightly sweet taste.

#### Assignment of interventions

2.7.4

##### Randomisation, stratification, allocation concealment, and blinding

2.7.4.1

Individuals eligible for participation will be randomly allocated to one of the four study arms by an independent researcher. Participants will be stratified based on: (i) Sex (male vs. female); (ii) LIBRA cognitive risk factor profile (medium risk: 2–3 points vs. high risk: ≥4 points); (iii) Combined age and education level (≥70 years or low education vs. 60–69 years with high education). High education is defined as *HBO associate degree* (Dutch: HBO; Hoger Beroepsonderwijs).

Study arms will be block randomised within each stratum using SAS (183) to ensure a balanced number of participants per study arm. To preserve blinding, each intervention group will be assigned a unique, randomly generated 4-digit code. A designated staff member, not involved in data analysis, will access group allocations to prepare the intervention materials. Supplements and placebo will be packaged in identical, non-transparent sachets to prevent identification. Breaking the randomisation code of an individual participant will be only be permitted in the case of a suspected unexpected serious adverse reaction, serious adverse event (SAE), or other medical indication as determined by a physician.

##### Strategies to enhance adherence and ensure intervention safety

2.7.4.2

The four investigational products are commercially available, food-grade, prepared in a food-grade environment, and safe for oral consumption. Persons who are allergic to any of the products are excluded from participation. Mild gastrointestinal side effects may occur due to dietary fibre supplementation, which will reduce over time. However, our chosen dosages are in accordance with previous studies indicating gastrointestinal tolerance. To reduce potential side effects and improve compliance, dosage of the fibres are halved and will be tapered-up, as described in the preceding section. Adherence will be monitored by compliance diaries, returned supplement counts at end study visits, and five phone calls throughout the study that will also serve to address any issues that arise.

##### Criteria for discontinuing or modifying allocated interventions

2.7.4.3

Participants are free to withdraw from the study for any reason and at any time. Investigators may withdraw a subject from the study for urgent medical reasons. Subjects will not be replaced after withdrawal, and a 15% drop-out rate is included in the sample calculation. The study will be prematurely terminated if the medically responsible investigator determines that a SAE might be related to the study, or a reassessment of risk and benefits is deemed necessary. If the study terminates abruptly, data collected up to the date of termination will still be analysed and results published in adherence to the Dutch “Central Committee in Research Involving Human Subjects” (CCMO) guidelines. The Medical Research Ethics Committee (MREC) and participants will be informed as soon as possible about the premature termination. Follow-up of participants will only take place in case of withdrawal for medical reasons.

##### Adverse events

2.7.4.4

All adverse events reported spontaneously by the subject or observed by the research staff will be recorded. All SAEs will be evaluated by the research physician and reported to the accredited MREC, within 7 days of first knowledge. The study may be prematurely terminated if the participant’s health or safety is under risk.

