### Study design and setting

2.2

The PRECODE study is a randomised, double-blinded placebo-controlled, four-armed parallel trial in older adults (60–79 years) with SCD+, with a duration of 26 weeks (Clinical trials identifier NCT06433037). Participants (*n* = 164) will be randomised by block-randomisation (based on sex, age, education and risk factor profile) in four different groups of equal size (*n* = 41). Either one of the following will be administered daily:

Placebo (Maltodextrin) – 7 g per day, divided over two dosages of 3.5 g.Chicory inulin – 12 g per day, divided over two dosages of 6 g.Resistant dextrin – 14 g per day, divided over two dosages of 7 g.Seaweed polysaccharide – 1 g per day, divided over two dosages of 0.5 g. (Seaweed will additionally contain 7 g (3.5 g per dose) of placebo as a volumetric and isocaloric filler.)

Participants will undergo assessments at baseline (*T*_1_), week 13 (*T*_mid_) and at study end (*T*_1_), after 26 weeks at the Division of Human Nutrition & Health (HNH) at Wageningen University (WUR) and the Gelderse Vallei Hospital (ZGV) in the Netherlands (Figure 3). Each participant will have four study visits in total: two at *T*_0_, and two at *T*_1_. In a subselection of participants (*n* = 80), there will be an additional mid-visit (*T*_mid_) in week 13, with five study visits in total. At *T*_0_ and *T*_1_ participants will first visit WUR for investigations and a week later visit ZGV for fMRI scanning. In the week between the visits, participants will collect two faecal samples, wear smartwatches and complete online questionnaires at home. The *T*_mid_ visit consists of a single visit to WUR only. To ensure compliance and to address any questions or concerns that arise during the intervention, five phone calls (10–15 min) will be made to participants during the course of the study.

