	Physical activity	x		x
Other questionnaires (not outcome measurements)				
(1) Dietary intake	Food Frequency Questionnaire (MIND-diet adjusted)	x	x	x
(2) Participation perception	Study participation perception			x
(3) Compliance diary		x	x	x
(4) General health questionnaires^3^		x		x
(5) Frailty questionnaire (FRAIL-tool)		x		x

^1^*T*_0_: baseline; *T*_mid_: mid-study visit, week 13 (subselection *n* = 80), *T*_1_: end visit, week 26. ^2^ In addition to completion at the three time points, the GSRS will be completed weekly for the first month, to evaluate responses to increased fibre intake. ^3^Population demographics, e.g., age, sex, risk factor profile (LIBRA), medical history, medication, supplement use, for females: information regarding gynaecological and obstetric history. At *T*_1_ a subselection of questions are filled again to determine any changes in health or medication use over the study period. MIND: Mediterranean-DASH diet Intervention for Neurodegenerative Delay.

**Table 4 tab4:** Overview of cognitive assessment questionnaires.

Assessment	Cognitive domains	Completion time	Timepoint^1^			
			S	*T* _0_	*T* _mid_	*T* _1_
Telephonic Interview for Cognitive Status (TICS-m)	Screening tool for cognitive disorders (e.g., MCI, dementia)	30 min	x			
Cognitive Failure Questionnaire	Perception of subjective cognitive decline	10 min		x	x	x
NTB						
Montreal cognitive assessment scale	Testing for light cognitive deterioration and global cognition	15 min		x		
Cognitive functional composite						
ADAS-Cog word recognition	Episodic memory	25–30 min in total		x	x	x
ADAS-Cog orientation	Episodic memory			x	x	x
ADAS-Cog word recall	Episodic memory			x	x	x
Digit symbol substitution test	Executive function			x	x	x
Digit span backward task	Working memory			x	x	x
Category fluency test	Executive function			x	x	x
Mood						
Geriatric depression scale (GDS-15)	Depression	7 min		x	x	x
Generalised anxiety disorder (GAD-7)	Anxiety	10 min		x	x	x

^1^S: Screening; *T*_0_: baseline; *T*_mid_: mid-study visit, week 13 (subselection *n* = 80); *T*_1_: end visit, week 26. ADAS: Alzheimer’s Disease Assessment Scale.

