#### Intervention start (week 1)

2.6.2

After the ZGV-*T*_0_ visit, the 26 week intervention starts. Subjects will consume the assigned dietary fibre supplement/placebo during breakfast and dinner. At five occasions, participants will receive a phone call to check compliance, address concerns, and to provide motivation if needed.

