##### Gastrointestinal questionnaires

2.8.2.2

Gastrointestinal symptoms will be assessed using the Gastrointestinal Symptom Rating Scale (GSRS) and the Bristol Stool Scale (BSS). The GSRS includes 15 items across five symptom clusters: abdominal pain, reflux, indigestion, constipation, and diarrhoea, scored from 1 (no discomfort) to 7 (very severe discomfort) (212). It is validated for use in healthy adults and has been applied to assess changes in gastrointestinal symptoms with increased fibre consumption (213). The BSS is a seven-point scale that categorises stool form, with Types 1–2 indicating constipation, Types 6–7 diarrhoea, and Types 3–5 considered normal. It includes pictorial representations and is widely used in clinical and research contexts (214). The GSRS will be completed at all study visits and weekly during the first month. The BSS will be completed with each faecal sample collection.

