The inclusion of a mid-study visit after 13 weeks, allows for determining the duration of intervention needed for microbiota and metabolite shifts. Furthermore, mid-study effects on cognition by NTB will allow for insights into timing of onsets of potential protective cognitive effects. Moreover, sex, ApoE genotype and age, influence AD disease stage progression (251). Here, further valuable information on whether these factors may influence the trajectory of potential interventions may be highlighted. Moreover, should there be any significant association evidenced between microbial compositional change and cognitive performance, it might be worthwhile to conduct a follow-up investigation, in which we research if and how long potential microbiota changes last after the trial has been finished, and to compare E4 vs. non-E4 carriers and relatedness of the number of LIBRA risk factors.

Despite its strengths, the study has potential limitations. The self-reported and progressive nature of SCD + may introduce heterogeneity, such as the potential inclusion of individuals with undiagnosed depression and anxiety that may mimic cognitive decline (114, 252). Clinical depression and anxiety are excluded at screening, and will be further assessed by GDS-15 and GAD-7 scores at baseline. Furthermore, some individuals may potentially convert to amnestic MCI over the course of the intervention, which will be evaluated by end-NTB results. Inclusion criteria, such as requirements for general and technological literacy, may additionally introduce bias towards individuals with higher education or better cognitive function. In addition, the inclusion criterion of at least 2 LIBRA risk factors next to presence of SCD may overall limit the generalizability of our findings to SCD individuals with fewer or different combinations of lifestyle risk factors, and should not be generalized to the entire preclinical AD spectrum. Next, long-term fibre supplementation in older adults with increased gastrointestinal sensitivity, may lead to study withdrawal, for which a 15% drop-out rate has been included. Strategies such as dose tapering, morning and evening dosing, and telephone check-ins are used to promote adherence. Furthermore, due to the scope of inclusion and exclusion criteria, including MRI compatibility, extensive recruitment efforts might be needed.

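### Adverse events are recorded passively, with no standard question stated for calls or visits, and about half the participants have no scheduled GSRS and no visit in weeks 5 to 24

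*Protocol article*

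**What the plan says.** **Recording rule.** Protocol article, section 2.7.4.4 (Adverse events): "All adverse events reported spontaneously by the subject or observed by the research staff will be recorded". The section names no other route into the adverse-event record.

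**Symptom scale.** Section 2.8.2.2 (Gastrointestinal questionnaires): "The GSRS will be completed at all study visits and weekly during the first month". Footnote 2 to Table 3 agrees: "In addition to completion at the three time points, the GSRS will be completed weekly for the first month". The three time points are baseline, week 13 and the end of the study.

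**Visits.** Section 2.2 (Study design and setting): "In a subselection of participants (*n* = 80), there will be an additional mid-visit". Everyone else has two baseline visits, before supplementation starts, and two end visits, which section 2.6.4 places in weeks 25 and 26.

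**Calls.** Section 2.6.2 (Intervention start): "At five occasions, participants will receive a phone call to check compliance, address concerns, and to provide motivation if needed". Section 2.7.4.2 adds that the calls also deal with problems as they come up. Section 2.2 gives their length as 10 to 15 minutes. The article gives neither the call weeks nor a symptom question.

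**End-of-study health questions.** Footnote 3 to Table 3 has some general health questions repeated at the end, to pick up changes in health or medication.

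**Named risk.** Sections 2.7.2 and 2.7.4.2 name gastrointestinal discomfort as the main side effect. The Discussion says that "long-term fibre supplementation in older adults with increased gastrointestinal sensitivity, may lead to study withdrawal".

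**The concern.** This is a collection rule that the article states, not a detail it leaves out. As worded, an event enters the record only if the participant raises it unprompted or staff notice it. For a participant without the mid-study visit, staff see nobody on treatment until week 25, so observation contributes little for most of the exposure. What remains is volunteering, in calls whose stated purposes are compliance, concerns and motivation.

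The scheduled gastrointestinal questioning is concentrated in the first month, and week 1 of that month is a build-up week: "participants only consume half of the daily dosage during the first week of the study". The Discussion's worry is about long-term use. Any statement about how well 26 weeks of each fibre was tolerated would rest on the adverse-event record and on GSRS data that are sparse in the middle of the intervention. Serious events are affected too, because the seven-day reporting period in section 2.7.4.4 runs from when the team first learns of the event.

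**Working it through.** The article gives no figure on this point to reproduce. The check is a count of scheduled contacts.

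**Inputs**
- Planned sample 164 and mid-study subset 80 (section 2.2).
- Randomised 151 (section 3, Initial results).
- Weekly GSRS in the first month, read here as weeks 1 to 4 (section 2.8.2.2 and Table 3).
- Mid-study visit in week 13 (section 2.6.3); end visits in weeks 25 and 26 (section 2.6.4).
- Half dosage in week 1 only (section 2.7.3).

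**Participants without the mid-study visit**
- As planned: 164 − 80 = 84, and 84/164 = 51%.
- As randomised: 151 − 80 = 71, and 71/151 = 47%. This assumes that the subset stayed at 80 although recruitment fell short; the article does not say.

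**Weeks without a scheduled GSRS**
- Without the mid-study visit: weeks 5 to 24, which is 24 − 5 + 1 = 20 of 26 weeks (77%).
- With it: weeks 5 to 12 (8 weeks) and weeks 14 to 24 (11 weeks).

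**Scheduled on-treatment contacts**

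| | Without mid-study visit | With mid-study visit |
|---|---|---|
| Visits | 2 (weeks 25, 26) | 3 (weeks 13, 25, 26) |
| GSRS completions | 4 weekly + 1 at end = 5 | 4 weekly + 1 mid + 1 at end = 6 |
| Phone calls | 5, weeks not stated | 5, weeks not stated |

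**Routes into the adverse-event record.** Four kinds of contact could reveal an event: GSRS, calls, visits and the end-of-study health questions. Section 2.7.4.4 mentions staff observation and spontaneous report. None of the sections describing the GSRS, the calls or the health questions says that an answer given there is entered as an adverse event.

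**The case against.** The best case for the plan has five parts.

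1. **The calls.** They take place during the intervention, are meant to deal with concerns, and appear in a section on adherence and safety that has just discussed gastrointestinal effects. Call scripts and weeks commonly sit in a full protocol, which is not shown. This stands in part. A reader might infer that nobody asks about gastrointestinal symptoms for 20 weeks, but the article shows only that no GSRS is scheduled then. The recording rule itself is nevertheless stated, and it is passive.

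2. **The GSRS.** It is a listed secondary outcome, put to every participant in every arm. Its weekly use falls in the adaptation period, and section 2.7.4.2 expects gastrointestinal effects to lessen with time. This stands as a reason to leave the GSRS schedule alone. It does not cover other events or events with later onset.

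3. **Memory.** Participants are selected for memory complaints, so a reader might infer that they under-report. The documents do not show this: a TICS-m score below 23 is an exclusion, and the mean baseline MoCA is 26.09 out of 30.

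4. **Comparison between arms.** A reader might infer bias. The arms are randomised and blinded, and nothing suggests that the mid-study subset is unbalanced by arm. An extra visit for some participants affects absolute counts, not necessarily the contrast.

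5. **Objectives.** Safety is not a stated objective, and no formal tolerability claim is planned. This limits the weight of the point but does not remove it, since adverse events will be recorded in a trial with a named side effect and an allowance for withdrawal.

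**Conclusion.** The point holds in limited form. The stated rule is passive, no standard adverse-event question is given for calls or visits, and no link is stated from GSRS, call or end-of-study answers to the adverse-event record. Between 47% (71 of 151, if the subset stayed at 80) and 51% (84 of 164 as planned) of participants have neither a scheduled GSRS nor a visit in weeks 5 to 24. Adverse-event counts over 26 weeks are therefore likely to be incomplete, and ascertainment differs between participants with and without the mid-study visit.

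The size of any under-capture cannot be computed from the documents, which give neither an event rate nor a capture rate for spontaneous reporting. Applying assumed rates to the whole 26 weeks would also ignore the direct questioning in month 1 and at the end.

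The primary analysis is not affected. The change is still worth making because it uses contacts that already take place. If the full protocol already contains a standard question, the article's wording should be brought into line with it.

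**What to change.** In section 2.7.4.4, replace spontaneous-only recording with solicited collection:

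- Put one standard open adverse-event question to every participant at each of the five planned calls and at every on-treatment visit.
- Fix the call weeks in advance, the same for all arms and for participants with and without the mid-study visit, with at least some calls after month 1.
- Enter answers in the adverse-event log with onset date, marked as solicited or spontaneous, and report the two kinds separately by arm.
- State whether GSRS and end-of-study health answers are entered as adverse events.
- Keep the GSRS schedule unchanged. Adding it to the calls would alter the frequency and mode of a secondary outcome during the trial.

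**Cost.** A few minutes in each 10- to 15-minute call, and more minor events recorded in every arm.

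**Timing.** Baseline was complete by July 2025, so some or all of the 26-week follow-up may already be past. Events before the change will be less completely captured. The report should give the date of the change and say so when tolerability is described. If no follow-up remains, that qualification is what is left to make.
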